### Identification, recruitment and consent procedures

All potential participants will be identified through the following methods: by their treating clinician who is a clinical member of the research team, in clinic at the Newcastle Diabetes Centre (applicable to those with diabetes only); via poster adverts in general practitioner (GP) practices and other secondary care clinics; GP practice database searches facilitated by the North East and North Cumbria Clinical Research Network; via social media; and via the Newcastle United Foundation charity. All methods have been reviewed and approved by the Health Research Authority and the study sponsor, through their ethical and governance review processes.

A participant information sheet will be sent to potential participants. Informed written consent will be given and eligibility confirmed by a member of the research team. Potential participants will then be screened with the Rockwood Clinical Frailty Score, by either their treating diabetes clinician (where applicable) or by a member of the research team. The study will take place from December 2020 to September 2022.

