### Aims and objectives

The purpose of this baseline case–control descriptive observational study and subsequent feasibility trial is to characterise the physical function, cardiovascular health, and the health and well-being of older people with mild frailty and with/without insulin-treated diabetes, and to test the feasibility of conducting a trial of resistance training in improving these parameters, and the acceptability of regular resistance exercise as a modality to improve health outcomes in older people with insulin treated diabetes.

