## Methods and analysis

### Study design

This is a single-centre interventional feasibility randomised controlled trial with an associated baseline case–control descriptive observational component, and a qualitative and process evaluation component, conducted in Newcastle upon Tyne, England. Thirty participants with insulin treated diabetes and mild frailty, and thirty without diabetes will be recruited. All participants will be aged ≥60. All participants will undergo blood and physical testing, for the baseline case–control component. The diabetic participants will then go forward into the trial. They will be randomised 1:1 to the intervention group, which is a 4-week programme of supervised resistance exercise training, or to the control group; to carry on with any usual activity as normal. The current version of the protocol is V.3.

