### Exclusion and inclusion criteria

Inclusion criteria for diabetes group (n=30):

Adults ≥60 years.Type 1 diabetes OR type 2 diabetes treated with exogenous insulin.BMI <30 in participants with type 2 diabetes.Rockwood Clinical Frailty Score of 3 or 4.

Inclusion criteria for non-diabetes group (n=30):

Adults ≥60 years.Rockwood Clinical Frailty Score of 3 or 4.

Exclusion criteria for all groups:

History of myocardial infarction, stroke, renal failure, severe hypertension or liver disease in the last 12 months.Unsuitable for the intervention due to limiting musculoskeletal problems.Inability to give written informed consent.

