### Sample size calculation

This is a feasibility study with no existing data to draw on to inform a meaningful sample size calculation. We have selected a sample size in line with previous guidance on feasibility studies,^42^ and data on key outcomes collected during this trial will inform the sample size calculation for a larger efficacy trial in future.

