### Data analysis plan

#### Quantitative analysis

This is a feasibility study to inform a larger trial and no hypothesis testing will be conducted. Consequently, quantitative data analysis will be descriptive. Mean, SD, range and 95% CI will be assessed on all quantitative data to assess response rates, numbers of individuals consented and randomised, retention rate, fidelity to the intervention, and participation in the training programme and qualitative interviews. The same descriptive methods will be used to report questionnaire and assessment data at baseline and 5 weeks. Statistical analyses will be conducted using IBM SPSS Statistics V.22 software.

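### The qualifying Rockwood score may be given by the treating clinician for some participants with diabetes but only by the research team for those without, so the baseline comparison may be partly mixed with assessor differences

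*Protocol article*

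**What the plan says.** The Aims and objectives section of the protocol article sets out to "characterise the physical function, cardiovascular health, and the health and well-being of older people with mild frailty and with/without insulin-treated diabetes". The groups for this are fixed under Study design: "Thirty participants with insulin treated diabetes and mild frailty, and thirty without diabetes will be recruited".

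Under Exclusion and inclusion criteria, each group must meet "Rockwood Clinical Frailty Score of 3 or 4". Apart from age 60 or over, this is the only inclusion criterion the two groups share. The exclusion criteria are common to all, and no matching is described.

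The section on identification, recruitment and consent says that the score is assigned "by either their treating diabetes clinician (where applicable) or by a member of the research team". Three other statements bear on this:

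- One recruitment route is through the clinic, where patients are identified by a treating clinician who also belongs to the research team. The other routes are posters, general practice database searches, social media and a charity.
- "Informed written consent will be given and eligibility confirmed by a member of the research team". The frailty screen is described after this step.
- The Quantitative analysis section states "no hypothesis testing will be conducted. Consequently, quantitative data analysis will be descriptive".

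**The concern.** The Rockwood score is a judgement, and it decides who enters each group and with what mix of 3s and 4s. The baseline measures then compared (isometric strength, walking speed, timed sit to stand) are closely related to frailty. A shift in how the score is given therefore moves the outcome as well as the entry threshold.

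A participant with diabetes may be scored by a clinician who already knows the history. A participant without diabetes cannot be, because no such clinician exists for them. The type of assessor, and the information behind the score, is thus partly tied to the group being compared. If treating clinicians tend to score higher than other assessors, they admit fitter cases, and a true deficit in the diabetes group would look smaller. If they tend to score lower, the deficit would look larger. A group mean with its confidence interval shows neither effect.

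At stake is the descriptive comparison of older people with and without insulin-treated diabetes, which is the first aim listed in the Abstract.

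**Working it through.** The article gives no figure to reproduce. It states no alpha, power, effect size or SD (Sample size calculation: "This is a feasibility study with no existing data to draw on to inform a meaningful sample size calculation"). It gives neither the share of cases scored by clinicians nor the agreement between assessors. The check is therefore one of text, followed by an illustration on assumed inputs.

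**Text**

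| | With diabetes | Without diabetes |
|---|---|---|
| Frailty criterion | Rockwood 3 or 4 | Rockwood 3 or 4 |
| Possible scorers | Treating diabetes clinician, or research team member | Research team member only |
| Scorer may be the patient's own diabetes clinician | Yes | No |

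**Precision of the baseline comparison**

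With 30 against 30, the 95% half-width in SD units is 1.96 × √(2/30) = 0.506. With the t quantile on 58 degrees of freedom it is 0.517.

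**Possible bias, by simulation**

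All inputs are assumptions:
- Latent frailty is normal, with mean 3 or 3.5 and SD 1.2.
- A person is eligible if the score rounds to 3 or 4.
- Function correlates with frailty at 0.4 to 0.6 in absolute value.
- Clinicians score 0.25, 0.5 or 1 level higher than the research team.
- Clinicians score 25%, 50% or 100% of cases.

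The result is the spurious group difference in function, in SDs of function among those eligible on the research-team score. Each range runs over the two correlations and the two means.

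| Clinician shift | 25% of cases | 50% of cases | 100% of cases |
|---|---|---|---|
| 0.25 level | 0.02–0.03 | 0.04–0.06 | 0.07–0.12 |
| 0.5 level | 0.04–0.06 | 0.07–0.12 | 0.14–0.23 |
| 1 level | 0.07–0.12 | 0.14–0.23 | 0.28–0.47 |

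With no systematic shift the bias is zero.

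**The same on the gait-speed scale**

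Assume that one Rockwood level corresponds to 0.10–0.20 m/s, that a net 20%–30% of cases are placed one level away in the same direction, and that the SD is 0.20 m/s.
- Bias: 0.20 × 0.10 = 0.02 m/s up to 0.30 × 0.20 = 0.06 m/s, that is 0.02/0.20 = 0.1 SD to 0.06/0.20 = 0.3 SD.
- Standard error of the difference: 0.20 × √(2/30) = 0.052 m/s.
- Ratio of bias to standard error: 0.39 to 1.16.
- 95% half-width: 1.96 × 0.052 = 0.10 m/s, so even the upper bias lies inside it.

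Disagreement in both directions would largely cancel, so these figures sit towards the high side.

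**The case against.** The strongest reply is that there is no clean split between clinicians and the research team. The article says that patients seen in clinic are identified "by their treating clinician who is a clinical member of the research team, in clinic at the Newcastle Diabetes Centre (applicable to those with diabetes" (the bracket goes on to restrict this route to them), and that a team member confirms eligibility. Cases who come by the other routes may well be scored by team members who do not treat them. The affected comparison is descriptive and not primary, and the bias needs a material share of clinician-scored cases together with a systematic difference in one direction. The article states neither. Weight loss, exhaustion and activity level are also recorded in everyone, which gives some description of frailty that does not depend on the scorer.

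Most of this stands, and it limits the point without removing it. A treating clinician who belongs to the team still has prior knowledge of the patient, and that exists for cases only. The text places confirmation of eligibility before the frailty screen and describes no second, common scoring. Reporting without tests does not correct a difference in how the groups were selected.

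A reader might infer that treating clinicians would stretch the score in order to recruit. The article says nothing of the kind, and any such incentive would apply equally to staff scoring people without diabetes.

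**Conclusion.** The point holds as a possibility written into the procedure. Cases may be scored by their own clinician and controls cannot be, so the baseline contrast in physical function may be partly mixed with assessor differences. The size cannot be known from the article. On the assumptions above it is about 0.02 to 0.23 SD for a quarter- to half-level shift. It reaches 0.28 to 0.47 SD only if every case is clinician-scored and the shift is a full level. All but these last values are below half of the 0.51 SD half-width.

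Two stronger readings are not supported. A reader might conclude that the baseline differences are in fact confounded by assessor, but no disagreement between assessors is documented. A reader might also conclude that the trial itself is compromised. Randomisation takes place within the diabetes group after scoring, so the comparison of arms is untouched, as are the primary feasibility outcomes. Nor does the article claim that the score makes the two baseline groups comparable; it is a shared entry criterion.

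This is a modest weakness in a secondary, descriptive aim, worth correcting because correction is cheap.

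**What to change.** In the section on identification, recruitment and consent, let treating clinicians pre-identify patients only. Have the same research-team assessor or assessors, and not the patient's treating clinician, assign the qualifying Rockwood score in both groups.

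Failing that, record who scored each participant and show the baseline comparison by assessor type. This is weaker. The like-for-like contrast would use only the cases not scored by their own clinician. If that were half of them, for illustration, the half-width would grow to 1.96 × √(1/15 + 1/30) = 0.62 SD.

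The main fix needs no extra staff, since the research team already scores every participant without diabetes. It costs a few more minutes per participant with diabetes, and some clinician-identified patients may not qualify on the common score.

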### Study procedures

#### Initial procedures

All 60 participants will undergo the following blood/cardiovascular, physical tests, and patient reported outcome measures at the Newcastle Clinical Research Facility, at the start of the trial and after the 4-week intervention/control period:

##### Blood and cardiovascular:

Resting blood pressure.A 15 mL blood sample will be taken via venepuncture for the quantification of: glycated haemoglobin (HbA1c), blood lipid profile, inflammatory cytokines by routine hospital clinical chemistry or Newcastle Laboratories. 5 mL will be used to assess counts of endothelial progenitor cells, by flow cytometry as previously described, for a deeper investigation of vascular health in this patient group.^38^

##### Physical function

Body composition: height, weight, waist circumference, % body fat and % fat free mass using bioelectrical impedance analysis (SECA 515 Body Composition Analyser).Isometric strength: a torque and strain gauge will be used to assess the force capability of the participants’ lower limbs. This test involves maximally extending the leg against an immovable strain gauge, this allows for the calculation of peak force and time-course changes in force.Isometric strength: a torque and strain gauge will be used to assess the force capability of the participants’ lower limbs. This test involves maximally extending the leg against an immovable strain gauge, this allows for the calculation of peak force and time-course changes in force.Gait speed: using digital timing gates, the participants will be required to complete three 4 m walking tests, to assess the normal walking speed of the participants.Timed Sit to stand: participants will sit on a chair and complete five stand and sit movements without use of the arms.

##### Patient-reported outcome measures

For all participants:

Health-related quality of life: the Short Form-36.

For participants with diabetes only:

Problem Areas in Diabetes scale.Hypo Fear Scale.

##### Clinical history

For all participants, information on:

Comorbid disease.Current medications, including changes in medications during the trial period.Weight loss.Exhaustion.Physical activity levels (using the International Physical Activity Questionnaire, short form).

For participants with diabetes only, information on:

Insulin regimen.Glucose monitoring (self-report).Serious hypoglycaemic episodes over the past 12 months.

### Randomisation

After completing the initial testing procedures, the diabetic group (n=30) will be randomised in a 1:1 ratio to either the intervention group (4-week supervised resistance training programme), or the control group (see figure 1).

**Figure 1 F1:**
[figure not shown]
Consolidated Standards of Reporting Trials diagram. BMI, body mass index; PROMS, patient reported outcome measures.

Randomisation of the diabetic group will take place at the end of the baseline visit. Randomisation will be done in a Good Clinical Practice (GCP)-compliant manner using a web-based randomisation system (http://www.randomization.com/). The allocation sequence will be prepared by individuals who will remain independent of the study team to preserve allocation concealment. The randomisation code sequence will not be accessible by the study team until after the trial analysis is complete.

### Intervention

The intervention is a 4-week, semistructured resistance exercise training programme, designed to increase muscle mass and strength. Training will be carried out at participants’ preferred public gym, and facilitated by a trained member of the research team. The programme involves 2–3 sessions lasting less than 1 hour each, per week, for each of the 4 weeks. Weeks 1 and 2 will be fully supervised by a member of the research team. In week 3, participants will be asked to train alone in one of the sessions, and in week 4, they will train fully independently. A 4-week programme has been selected to assess feasibility and acceptability to participants, similar to previous feasibility work carried out in our team with older people.^36^ The programme is not designed to induce changes in any physical or clinical outcomes.

The trial will be carried out once all relevant COVID-19 restrictions have been lifted in England. The research team will also adhere to COVID-19 standard operating protocols specified by the sponsor.

#### Resistance exercise training programme design

Following extensive explanation and demonstration of proper exercise technique. For each exercise, resistance is increased until momentary failure occurs within 10 repetitions. One repetition maximum (1RM) is estimated using a prediction equation based on using the variables of ‘load lifted’ and ‘number of repetitions completed’.^39^ This method has been previously demonstrated as a valid approach for estimating 1RM in older people.^40^

The following exercise sessions will be completed weekly for 4 weeks:

##### Session 1

Leg press, leg extension, leg curl, leg adduction, calf raises, chest press, shoulder press, lateral pull down, lateral raises.

Repetitions: 8–12 at 70% 1RM, Sets per exercise: 3, recovery between sets: 2 min.

##### Session 2

Leg press, single-leg half leg press, chest press, shoulder press, seated row.

Repetitions: 5–8 at 85% 1RM, Sets per exercise: 3, recovery between sets: 4 min or feeling recovered.

##### Session 3

Leg press, leg extension, leg curl, leg adduction, chest press, shoulder press, lateral pull down, lateral raises.

Repetitions: 12–15 at 60% 1RM, Sets per exercise: 3, recovery between sets: 2 min.

### Control arm

Participants randomised to the control arm will be asked to carry on with normal daily activities, without any changes to any exercise they might do.

### Blinding

Blinding will not be possible for participants as the intervention involves undertaking a supervised exercise resistance training programme, with the control arm undertaking no additional exercise other than any usual level of activity. The clinical team, and the research staff responsible for analysing quantitative outcomes, will be blinded to treatment allocation. Research staff responsible for supervising the resistance training, and the qualitative aspects of the study, will not be blinded.

### Qualitative process evaluation

We will use qualitative methods to develop an in-depth understanding of participant perceptions and experiences on the following topics: age and frailty, physical activity, living with diabetes (where relevant), barriers and facilitators to participating in the study and resistance training more generally, and views on the resistance training programme (where relevant). Prior to the intervention commencing, one semistructured interview will be conducted with up to 20 participants. These will be split equally between the intervention group and control group, and between those with and without diabetes. We will then interview up to 10 intervention group participants after the 4-week training programme, to understand their views and experiences of the programme and perceived impact on their health and well-being. We will also offer participants the option of taking part in this interview as a one-off procedure, without taking part in the trial, should the trial be severely impacted by the COVID-19 global pandemic. We expect each interview to last 45–60 min. Interviews will take place at a time and location most suitable for the participants, either face to face or over the telephone. All participants will be approached for interview in order of recruitment. We anticipate that the sample sizes described will allow data saturation, and interviews will cease once no new semantic codes are identified from our concurrent thematic analysis of these data (code saturation).^41^

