**Methods and analysis:**

Thirty adults aged ≥60 years with insulin-treated diabetes mellitus (type 1 or 2), and 30 without, all with mild frailty (3–4 on the Rockwood Frailty Scale) will be recruited. All will complete blood, cardiovascular and physical function testing. Only the diabetic group will then proceed into the trial itself. They will be randomised 1:1 to a 4-week semisupervised resistance training programme, designed to increase muscle mass and strength, or to usual care, defined as their regular physical activity, for 4 weeks. This group will then repeat testing. Primary outcomes include recruitment rate, attrition rate, intervention fidelity and acceptability, and adherence to the training programme. A subset of participants will be interviewed before and after the training programme to understand experiences of resistance training, impact on health and living with diabetes (where relevant) as they have aged. Analyses will include descriptive statistics and qualitative thematic analysis.

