### Study outcomes

#### Feasibility outcomes

The primary aim of this study is acceptability and feasibility of procedures for recruitment and retention, randomisation and adherence and fidelity to the resistance training programme intervention. We will use a traffic light approach, where green=proceed without modification; amber=proceed but with modification, red=unrealistic to proceed without major modification. Recruitment rates will be calculated as the rate of invited participants who are eligible, who subsequently provide informed consent. Green ≥50% recruitment, amber=25%–50% recruitment, red ≤25% recruitment. Attrition rates will be measured, defined by discontinuation of the resistance training intervention and/or lost to follow-up measurement for both conditions. Green ≤10% attrition, amber=10%–20% attrition, red ≥20% attrition. Reasons for attrition will be explored qualitatively. Acceptance, adherence and fidelity to the resistance training intervention will be monitored by the research team, who will measure session attendance: green ≥90% attendance, amber=75%–90% attendance, red ≤75% attendance, plus participant following intervention instructions >75% of the time, and participant self-report. Preintervention and postintervention qualitative interviews will be used to assess the acceptability of the resistance training intervention, influences on diabetes self-management where applicable, and well-being more generally, at baseline and at 5 weeks. Information about adverse events will be collected for the intervention group.

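### The two equal splits of the pre-programme interviews cannot both hold, and post-programme interviews in order of recruitment do not ensure that those who stop training are heard

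*Protocol article*

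**What the plan says.** Under Qualitative process evaluation, the protocol article sets two rounds of interviews.

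- Before the programme: "Prior to the intervention commencing, one semistructured interview will be conducted with up to 20 participants". The sample is then divided two ways: "These will be split equally between the intervention group and control group, and between those with and without diabetes".
- After the programme: "We will then interview up to 10 intervention group participants after the 4-week training programme".
- Order of approach: "All participants will be approached for interview in order of recruitment". Interviewing stops at code saturation.

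On who has an arm, the Abstract says "Only the diabetic group will then proceed into the trial itself", and the Randomisation section says "the diabetic group (n=30) will be randomised in a 1:1 ratio". The Control arm section describes that arm as people randomised to it.

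On the use of the interviews, Feasibility outcomes says "Reasons for attrition will be explored qualitatively" and uses the interviews before and after the programme to assess acceptability. The Qualitative analysis section compares intervention with control participants and undertakes to look actively for deviant cases.

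**The concern.** The first problem is an internal contradiction. An equal division by arm presupposes that every interviewee has an arm. Half of the study population, the 30 people without diabetes, has none. Interview staff could resolve the sentence in different ways, and the intervention-versus-control comparison in the Qualitative analysis section would differ accordingly.

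The second is a mismatch between a sampling rule and its purpose. The people who can best explain attrition are those who stop training, and they are likely to be few. A consecutive approach with a ceiling of 10 out of 15 leaves it to chance whether each of them is reached. Attendance and attrition counts show how many stop. The reasons, which a decision to proceed with modification would need, have to come from the qualitative work.

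**Working it through.** **The pre-programme split.** Inputs: up to 20 interviews (Qualitative process evaluation); 30 with diabetes randomised 1:1, so 15 per arm (Randomisation); 30 without diabetes and in no arm (Exclusion and inclusion criteria). Let I and C be interviewees with diabetes in the intervention and control arms, and N those without diabetes, with I + C + N = 20.

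- Both splits over all 20: I = C = 10 and N = 10 gives a total of 30, not 20. There is no solution.
- Split by arm over all 20: I = 10, C = 10, N = 0. Nobody without diabetes is interviewed.
- Nested split: N = I + C and I = C gives I = 5, C = 5, N = 10. All three groups are filled.
- People without diabetes counted as controls: I = C + N and I + C = N gives I = 10, C = 0, N = 10. No randomised control is interviewed, and the arm comparison becomes a comparison by diabetes status.

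The nested split is workable in practice: randomisation takes place at the end of the baseline visit, so arm can be known before the programme starts.

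**The post-programme interviews.** Inputs: 15 in the training arm, 10 interviewed. Let d be the number who stop training. The plan gives no expected d. Its red line for attrition is 20%, which in this arm would be 3 of 15; 2 and 5 are shown for range. Assume that recruitment order is unrelated to stopping and that everyone approached agrees. The number of stoppers among the 10 is then hypergeometric, with C(15,10) = 3003 equally likely sets:

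- expected number missed = d × 5/15
- P(none heard) = C(15−d, 10)/3003
- P(at least one missed) = 1 − C(15−d, 10−d)/3003

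| Stoppers of 15 | Expected missed | P(none heard) | P(at least one missed) |
|---|---|---|---|
| 2 | 0.67 | 286/3003 = 9.5% | 1 − 1287/3003 = 57.1% |
| 3 | 1.00 | 66/3003 = 2.2% | 1 − 792/3003 = 73.6% |
| 5 | 1.67 | 1/3003 = 0.03% | 1 − 252/3003 = 91.6% |

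**If stoppers are likelier to decline.** Take d = 3, let all 12 completers agree, and let each stopper agree with probability p (an assumption). With A the number of willing stoppers, A ~ Binomial(3, p), and P(none heard) is the sum over a of P(A = a) × 66/C(12+a, 10). The ratios for a = 0, 1, 2, 3 are 1, 66/286 = 0.231, 66/1001 = 0.066 and 66/3003 = 0.022.

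- p = 0.5: 0.125×1 + 0.375×0.231 + 0.375×0.066 + 0.125×0.022 = about 24%
- p = 0.3: 0.343×1 + 0.441×0.231 + 0.189×0.066 + 0.027×0.022 = about 46%

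If code saturation ends interviewing before 10, the chance of missing a stopper is larger still.

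**The case against.** On the split, the nested allocation is feasible and may well be what was meant, and 20 is a ceiling. That stands: the sentence needs clarifying, and the interviews can be done.

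On the post-programme interviews, a reader might infer that order of recruitment favours completers and so biases acceptability upwards. The documents do not support this. The rule covers all participants, and someone who stops training remains in the intervention group. The phrase about the 4-week programme gives the timing of the interview and sets no condition of completion. Nothing links early recruitment to good attendance. Under a neutral order the chance of hearing no stopper at the 20% line is only 2.2%; silence from all of them would require a further assumption, such as completers alone being interviewed. Nor does acceptability rest mainly on interviews: Feasibility outcomes also uses attendance, following of instructions and self-report, and no traffic-light threshold uses interview data.

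The commitments to explore attrition and seek deviant cases also suggest that the team intends to speak to people who stop, and the full protocol, not shown, may say how. What remains is that the sampling rule in the article does not deliver those commitments by itself, and an order-of-recruitment rule gives no means of seeking out particular cases.

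A reader might also object that, under the nested split, at most 5 of the 10 post-programme interviewees could have been interviewed beforehand. The plan never promises paired interviews, so this is not a defect.

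**Conclusion.** Two limited points hold. First, the two equal splits contradict the design if both apply to all 20 interviews, because arm exists only among participants with diabetes; this follows from the text without assumptions. Second, the post-programme rule does not ensure that people who stop or attend poorly are heard. At 3 stoppers of 15, one is expected to be missed and at least one is missed with probability 73.6%, assuming that order is unrelated to stopping, that all agree and that all 10 interviews take place. The 24% to 46% chance of hearing none depends on assumed agreement rates of 50% and 30% that no document supplies. No direction or size of bias in acceptability is shown. The second point is an inexpensive improvement in line with the plan's own aims; it does not invalidate the trial's feasibility criteria.

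**What to change.** State the three cells: up to 10 interviewees without diabetes and up to 10 with diabetes, 5 from the intervention arm and 5 from the control arm, approached in order of recruitment within each cell. Taking all 10 with diabetes from the training arm would not be a good substitute, since it removes the control interviews that the plan's own comparison needs.

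For the post-programme interviews, first invite every intervention participant who discontinued training or attended 75% of sessions or fewer, borrowing the plan's red attendance band as an individual cut-off. Then fill the remaining places in order of recruitment, within the same total of up to 10. Do not apply the saturation rule until those in the first group have been invited.

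The cost is a few sentences; the number of interviews and the quantitative plan are unchanged. There are two drawbacks. Some who stop will decline, so the rule improves the chance of hearing them without guaranteeing it. The interviewed group will also over-represent stoppers and low attenders, so themes should be reported by completion status and not read as typical of the arm.
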